## Abstract

**Background:**

In sub-Saharan Africa, HIV care is dependent on informal caregiving, typically by female family members. Informal caregiving has been associated with numerous negative effects on caregivers (i.e., depression, intimate partner violence (IPV), financial insecurity). These factors impact caregivers’ ability to provide care and their own wellbeing. South Africa is home to approximately 17% of the world’s children and adolescents living with HIV (CALHIV), making the development of initiatives that mitigate the negative effects of caregiving critical. This protocol details the design of a cluster randomized trial seeking to assess the feasibility, preliminary effectiveness, cost-effectiveness, and acceptability of a cash transfer plus gender transformative economic empowerment intervention for improving psychological wellbeing, depressive symptoms, gender equality, and economic outcomes of caregivers of CALHIV.

**Methods:**

Caregivers of CALHIV will be recruited from public sector HIV clinics within the eThekwini Municipality, KwaZulu-Natal, South Africa. Clusters will be randomly assigned to intervention or control groups. Participants in the intervention arm (*n* = 120) will receive cash transfers (ZAR350, USD $18.79) and enroll in a program (10 workshop sessions) over a 6-month period. Participants in the control arm (*n* = 120) will receive a monthly cash transfer (ZAR350, USD $18.79) for a 6-month period and a once-off standard mobile message, encouraging linkage to healthcare services. Participants will be interviewed at baseline and endline, at the 7-month mark, to collect socio-demographic, health and wellbeing status, IPV, costs and earnings, and food security data. The primary outcomes include consent rate, overall retention rate, workshops retention rate, cash transfer protocol adherence, staff perceptions on implementation, psychological wellbeing, depressive symptoms, and IPV. A qualitative study and economic evaluation will be conducted alongside the main trial to probe participant perceptions of the intervention and assess cost and cost-effectiveness.

**Discussion:**

This trial has the potential to inform a larger confirmatory trial which will be valuable for informing post-pandemic recovery efforts for caregivers of CALHIV and others disproportionally burdened by compounding health and social crises.

**Trial registration:**

PACTR202311618532061. Registry name: Pan African Clinical Trial Registry (PACTR), retrospectively registered on November 21, 2023; The first participant was enrolled on August 24, 2023.

**Supplementary Information:**

The online version contains supplementary material available at 10.1186/s40814-025-01643-3.

## Background

South Africa has the largest HIV epidemic globally, with approximately 17% of the estimated 2.58 million children and adolescents living with HIV (CALHIV) living there and thus a similar number of caregivers [1]. Supportive caregivers are critical to the health and wellbeing of CALHIV [2]. HIV care for CALHIV in resource-poor settings is highly dependent on informal caregiving, usually delivered by a mother or female family member [3]. However, informal caregiving has been linked to numerous negative effects on the caregivers themselves. Unpaid caregiving is associated with depression and intimate partner violence (IPV) and can result in long-term negative economic consequences [4, 5]. Moreover, as informal caregiving is highly gendered and often occurs in lower income households, these negative impacts are amplified by social inequities such as gender and income inequality [6]. These factors impact both caregivers’ own wellbeing and their ability to provide quality care to CALHIV [2].

The COVID- 19 pandemic magnified gender and income inequalities and is predicted to have a long-term health and socio-economic impacts [7, 8]. To mitigate the economic impacts of the COVID- 19 pandemic restrictions on the most vulnerable, the South African government implemented the COVID- 19 Social Relief of Distress (SRD) grant [9]. Introduced in May 2020 and set to continue as a basic income grant in the future, this social grant comprises a monthly ZAR 350 payment (USD $18.79) delivered over a 6-month period [9]. Modeling studies have noted the benefits grants such as the SRD grant could have on the wellbeing of the most marginalized, including unpaid workers, during pandemic recovery and if made permanent [10–12]. However, while the United Nations Development Programme’s strategy for pandemic recovery has incorporated enhancing social protection into the next phases of its COVID- 19 crisis response, there is a notable lack of empirical research on pandemic recovery strategies and social protection in South Africa [12]. There is a need to enhance national efforts surrounding pandemic recovery strategies and ensure approaches empower the most vulnerable.

The wellbeing of women caregivers of CALHIV in South Africa can be improved through strategies that strengthen their economic livelihoods by enabling women to generate income, improve self-esteem, achieve valued social status, and increase autonomy and control over their lives through access to resources [13–15]. In 2021, our team piloted a randomized controlled trial of an economic incentive package intended to improve the wellbeing of caregivers of adolescents living with HIV in KwaZulu-Natal, South Africa, during COVID- 19 by addressing key barriers (CWeL trial) [16]. The economic incentive package comprised a monthly ZAR350 (USD $18.79) cash transfer paired with motivational text messages that promoted caregiver wellbeing and were delivered over a 3-month period [16]. The CWeL trial was associated with increases in psychological wellbeing and decreases in depressive symptoms and had a significant effect on reducing caregiver-related distress [16]. Furthermore, caregivers expressed the need for group-based psychosocial and economic empowerment support to enhance the intervention [16]. Group-based economic empowerment training interventions are another approach to strengthening livelihoods [17]. When economic empowerment interventions are combined with components seeking to transform gender roles to ones that are more equitable, termed gender transformative approaches, group-based economic empowerment training interventions can reduce women’s experiences of IPV and gender inequalities by addressing the power dynamics, social norms, attitudes, and social systems that underlie them [17–20]. Stepping stones and creating futures (SSCF) is a group-based gender transformative + economic livelihoods intervention that aims to address multiple drivers of IPV amongst youth in KwaZulu-Natal, South Africa, by transforming gender attitudes and strengthening livelihoods [17]. In a large randomized controlled trial led by the team, SSCF was associated with significant improvements in women’s livelihoods, and for those who attended more sessions, reductions in depressive symptoms [17]. Following on from and building off the CWeL trial and SSCF trial, the Caregiver Wellbeing Plus (CWeL +) project aims to co-develop a cash transfer plus (+) gender transformative economic empowerment intervention for improving the psychological wellbeing (positive mental health), gender equality, and economic outcomes of caregivers of CALHIV in KwaZulu-Natal, South Africa. As per the SSCF intervention, the economic empowerment program of the CWEL + intervention will be delivered to groups of caregivers from sampled clinics. Hence, a cluster-randomized trial (CRT) would be an appropriate evaluation design to assess the effects of the CWEL + intervention. However, full-scale CRTs are expensive for resource constrained settings and careful planning is needed. Thus, we will conduct a pilot CRT to understand the feasibility of implementing a larger trial of this nature, the applicability of the intervention to caregivers, and to obtain preliminary clinical outcome data to inform the design and sample size of a future full-scale trial [21].

### Objectives

To co-develop a gender transformative economic empowerment intervention and a cash transfer to women caregivers of CALHIV.To assess the feasibility of this intervention in terms of key trial processes in the intervention and control arms.To describe participants’ views on the acceptability of delivery, content, safety, and utilization of the intervention versus control activities.To understand the mechanisms through which the intervention works to improve psychological wellbeing, economic empowerment, and experiences of gender inequity.To estimate the potential effect size of this intervention on key indicators to inform future trial design (improvements to psychological wellbeing, positive gender attitudes and earnings, and decreases in depressive symptoms and IPV) amongst caregivers of CALHIV.To measure the cost and cost-effectiveness of this intervention.

## Methodology

Reporting and methodology for the proposed study follow the Standard Protocol Items Recommendations for Interventional Trials (SPIRIT) [22] (see Fig. 1) and the Consolidated Standards of Reporting Trials (CONSORT)—extension to randomized pilot and feasibility trials [23] (see Additional file 1).

**Fig. 1 Fig1:**
[figure not shown]
Standard protocol items: recommendation for intervention trials (SPIRIT) flow diagram

### Design

This will be a two-arm CRT comprising a quantitative survey, an economic evaluation, and a qualitative sub-study. Clusters (public-sector HIV clinics) will be randomized into an intervention arm (*N* = 10 cluster) and a control arm (*N* = 10 clusters).

### Setting and cluster eligibility

This study will be conducted in the largely peri-urban eThekwini Metropolitan Health District, in KwaZulu-Natal, South Africa. The eThekwini municipality includes a sampling frame of 35 government (public sector) HIV clinics within primary healthcare clinics, community healthcare centers, and outpatient hospital-based facilities. Approximately *N* = 20 HIV clinics (clusters) will be sampled. Clusters within a 25-km radius of the field office, providing antiretroviral therapy to *n* > 1000 patients, and previously involved in the CWeL or SSCF trials will be eligible to participate in this trial. Clusters who are already enrolled in an existing CRT mental health or gender-based violence (GBV) intervention will be ineligible for participation. Two clinics from nearby wards (geopolitical sub-divisions) will be selected and randomly assigned to the intervention or control arm.

### Participant eligibility criteria

Participants will be recruited from the *N* = 20 clusters (approximately 12 participants per clinic resulting in 120 participants per arm). Eligible participants for this trial will be adult (18 +) women primary caregivers of CALHIV (aged 5–19 years) who are eligible for South Africa’s COVID- 19 SRD grant but are not currently receiving it, have access to a mobile phone, and provide informed consent. See Additional file 2 for SRD grant eligibility criteria.

### Participant recruitment

Caregivers of CALHIV who are not receiving a COVID- 19 SRD grant will be identified by clinic staff on the day of their routine HIV care appointment. Clinic staff will then refer potential participants to trial fieldworkers, who will conduct a face-to-face preliminary screen, during or after their clinic appointment to ensure eligibility criteria are met. Potentially eligible participants will be invited to the trial’s field office whereby fieldworkers will explain the study in participants’ preferred language and verify their understanding of the study using a comprehension checklist, detailing challenges, randomization, and consent procedures. Should caregivers have a good understanding of the study and provide written consent, they will be enrolled in the trial.

### Baseline and endline assessment

After the screening, female field staff will administer a baseline questionnaire to participants in their preferred language (English or isiZulu) (see Additional file 3). Seven months post-intervention, an endline assessment will be conducted. The questionnaires will ask about participant demographics, health-related quality of life, psychological wellbeing, depressive symptoms, IPV, gender attitudes, gender equality, economic empowerment, costs and earnings, food security, stigma and discrimination, and social support. The endline questionnaire will repeat all measures and also feature a module to probe participant’s perceptions and experiences of the trial. Data from these questionnaires will be captured on REDCap (v11.0.3) using electronic tablets [24, 25].

### Cluster randomization

Approximately 20 clusters will be recruited, with 12 participants per cluster and 10 clusters per arm resulting in 120 participants per arm. For each selected ward/s, the statistician will use a random number generator to assign one cluster to the intervention arm and one cluster to the control arm.

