#### Sample size justification

The chosen sample size of 240 participants was informed by findings from a related economic incentive trial with caregivers of CALHIV [16]. This sample size will enable us to estimate retention of 85% (with *n* = 36 participants or less declining participation or lost to follow-up) to within a 5% margin of error with 95% confidence [16]. In our previous pilot trial, we recruited caregivers (regardless of COVID- 19 SRD grant status) over a 2-month period with a retention rate of 85% at follow-up [16]. This suggests that a sample size of *n* = 240 potentially eligible caregivers for this trial could be recruited and retained within timeframe. Moreover, 10 clusters per arm are within the trial budget.

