### Statistical analysis

All statistical analysis will be performed using Stata V18.0 [38]. Baseline participant characteristics will be presented using descriptive statistics, including means, medians, and interquartile ranges. Feasibility outcomes will be analyzed using simple descriptive statistics (proportions) and results compared by arm. Linear mixed-effects models will be used for endline scores, adjusting for baseline scores and clustering. To account for the small number of clusters, the Satterthwaite correction will be applied to adjust the degrees of freedom in the linear mixed-effects models [39]. For all binary outcomes, depending on the prevalence of the outcome, we will use mixed effects logistic regression for prevalence less than or equal to 10% and log-binomial or robust Poisson regression when the outcome is common. The number of participants who completed baseline and endline interviews and attendance will be ascertained at each workshop to determine the retention rate.

For the economic evaluation, a breakdown of the total financial and economic costs for key cost categories will be presented to assess the feasibility of the trial, stratified by arm. The average cost per participant will be presented by the outcome. Costs will be presented in 2023 ZAR and USD and adjusted for inflation.

For the qualitative study, electronic audio files will be transcribed and verified by a study team member. A codebook will be developed and transcripts will be coded, with codes grouped into categories and, in turn, themes [40]. An intersectional analysis of the experiences of caregivers will be conducted by heeding stories of the ways intersecting identities shaped experiences during the pandemic [41]. Qualitative data will be used to illuminate preliminary patterns identified in the quantitative data and probe feasibility measures for the trial.

The team of investigators will be consulted to assess whether the hypothesized theory of change [27] was supported by the quantitative and qualitative data and to determine staff perceptions on project implementation; this will allow for the theory of change to be refined and strengthened and to assess the feasibility of the trial (see Table 1 for the study timeline).

**Table 1 Tab1:** Study timeline

	**Months 1–3**	**Months 4–6**	**Months 7–9**	**Months 10–12**	**Months 13–15**	**Months 16–18**	**Months 19–21**	**Months 22–24**

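### Clinics are randomised within nearby-ward pairs, but the stated models have no pair term, so arm-effect intervals are too wide if nearby clinics resemble each other

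*Protocol article*

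**What the plan says.** The Protocol article, under Setting and cluster eligibility, says: "Two clinics from nearby wards (geopolitical sub-divisions) will be selected and randomly assigned to the intervention or control arm". Under Cluster randomization, a random number generator is used for each selected ward or set of wards to "assign one cluster to the intervention arm and one cluster to the control arm". The same section gives about 20 clusters, "with 12 participants per cluster" and "10 clusters per arm resulting in 120 participants per arm". Together these describe about 10 pairs of clinics, with one clinic of each pair in each arm.

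Under Statistical analysis: "Linear mixed-effects models will be used for endline scores, adjusting for baseline scores and clustering". For the small number of clusters, "the Satterthwaite correction will be applied to adjust the degrees of freedom in the linear mixed-effects models". For binary outcomes, "we will use mixed effects logistic regression for prevalence less than or equal to 10% and log-binomial or robust Poisson regression", the latter two when the outcome is common. No ward, pair or stratum term is named for either type of outcome, and no reason is given for leaving one out.

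**The concern.** Pairing before randomisation balances the arms on whatever the two clinics of a pair share. That shared variation therefore cannot contribute to the true sampling error of the arm contrast. A model with a clinic random effect but no pair term still counts it as between-clinic variance and charges it to the standard error. The Satterthwaite method does not repair this, because it works from the variance structure in the fitted model. With 20 unpaired clusters it gives about 20 − 2 = 18 degrees of freedom, whereas a within-pair comparison has about 10 − 1 = 9.

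What is at stake is precision. One stated objective is to estimate potential effect sizes to inform a future trial, and with 20 clinics the intervals will be broad in any case. Needlessly wide ones make those estimates less useful.

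**Working it through.** **The plan's own figure.** The only precision figure in the article is for retention. At 85% and n = 240 the margin is 1.96 × √(0.85 × 0.15 / 240) = 4.5%. At 240 − 36 = 204 completers it is 4.9%. Both are within the stated 5%, and 15% of 240 is 36, so the figure reproduces as simple-random-sample precision. It does not involve the arm contrast and is untouched by this point.

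**Inputs for the arm contrast.** From the article: 10 pairs and 12 participants per clinic. Assumed, because the article gives neither: the ICC (0.01, 0.05, 0.10) and the share *s* of between-clinic variance that is common to a pair (0 to 0.75). The total SD is set to 1.

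**Formulas.**
- Variance of a clinic mean: V = ICC + (1 − ICC)/12.
- Part that differs within a pair: W = ICC(1 − s) + (1 − ICC)/12.
- True standard error of the arm contrast under paired allocation: √(2W/10).
- Standard error expected when the pair is ignored: √(2V/10).
- Overstatement: √(V/W). Correlation of the two clinic means in a pair: 1 − W/V.

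**Worked cases.**
- ICC 0.05, s = 0.5: V = 0.05 + 0.95/12 = 0.1292 and W = 0.025 + 0.0792 = 0.1042. The standard errors are 0.161 (pair ignored) and 0.144 (true), a ratio of 1.11.
- ICC 0.10, s = 0.5: V = 0.10 + 0.90/12 = 0.175 and W = 0.05 + 0.075 = 0.125. The standard errors are 0.187 and 0.158, a ratio of 1.18.

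**Simulation.** Clinic means were simulated 100,000 times per setting. The table compares an unpaired t interval (18 df) with a paired one (9 df). Half-widths are means, in SD units.

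| ICC | s | pair correlation | SE ratio | half-width, pair ignored | half-width, pair included | coverage, pair ignored |
|---|---|---|---|---|---|---|
| 0.01 | 0 | 0 | 1.00 | 0.282 | 0.299 | 95.1% |
| 0.01 | 0.75 | 0.08 | 1.04 | 0.282 | 0.287 | 95.9% |
| 0.05 | 0 | 0 | 1.00 | 0.333 | 0.354 | 95.0% |
| 0.05 | 0.25 | 0.10 | 1.05 | 0.333 | 0.336 | 95.9% |
| 0.05 | 0.5 | 0.19 | 1.11 | 0.333 | 0.317 | 96.9% |
| 0.05 | 0.75 | 0.29 | 1.19 | 0.333 | 0.298 | 97.7% |
| 0.10 | 0.25 | 0.14 | 1.08 | 0.388 | 0.381 | 96.4% |
| 0.10 | 0.5 | 0.29 | 1.18 | 0.387 | 0.348 | 97.6% |
| 0.10 | 0.75 | 0.43 | 1.32 | 0.387 | 0.311 | 98.6% |

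Type I error is 100% minus coverage, so 3.1% at ICC 0.05 and 2.4% at ICC 0.10 when half is shared. The paired interval covered 94.8% to 95.1% throughout.

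**Break-even.** The t quantile on 9 df is 1.077 times that on 18 df, so by quantiles alone pairing shortens the interval when the pair correlation exceeds 1 − 1/1.077² ≈ 0.14. On mean half-widths the penalty is 0.354/0.333 = 1.06, which puts break-even slightly lower, at 1 − (0.333/0.354)² ≈ 0.12. When pairs share nothing, the cost of pairing is thus about 6% in width.

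**Check on individual data.** Mixed models fitted by REML (150 runs per setting, so only indicative) agree. At ICC 0.10 and s = 0.75 the mean standard error was 0.182 with clinic only and 0.142 with pair as a fixed effect, against an empirical SD of 0.139.

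**The case against.** **The article is condensed.** It does not say that the pairing will be ignored, and an analysis plan that is not shown may include the term. That is fair, and a reader who infers a decision to discard the pairing goes beyond the text. But the article does not leave the model open. It names an adjustment set and a degrees-of-freedom method, and these do not match the allocation it describes. If a fuller plan has the term, the article should be aligned with it.

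**The effect is conditional.** A reader might infer that the intervals are certainly the wrong width. The documents do not support this. No ICC or pair correlation is given, and at ICC 0.01, or at ICC 0.05 with a quarter shared, including the pair makes the interval slightly wider. This stands, and it limits the claim.

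**The simulation is simpler than the planned model.** Adjusting for baseline score may absorb some stable ward-level differences, and the simulation has no baseline covariate. It also uses 12 per clinic, while Trial status reports 149 and 124 enrolled at baseline. Both points stand, so the figures illustrate the size and do not predict it.

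**The error is on the safe side.** It never produced coverage materially below 95%, and in the balanced case without covariates the arm estimate itself does not change. A reading in which the plan inflates false positives or biases the effect is therefore wrong.

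**The next trial may not be paired.** Nothing in the article says that it will be, and ten pairs would estimate a pair correlation poorly. It would be too much to say that the future design needs that correlation from this pilot.

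**Conclusion.** The mismatch is in the text: allocation is one-to-one within about 10 nearby-ward pairs, and the stated models omit the pair. If nearby clinics resemble each other, the arm-effect standard errors and intervals are too wide. Under the assumed ICCs of 0.05 and 0.10, with 25% to 75% of between-clinic variance shared, the standard error is overstated by a factor of 1.05 to 1.32 and coverage rises to between 95.9% and 98.6%. If pairs share little, or the ICC is near 0.01, the unpaired analysis is close to nominal and little is lost. The point concerns lost precision in effect estimates that are meant to inform a later trial. It does not touch the validity of the comparison or the retention-based sample size. It is worth correcting because analysing by the units within which the trial randomised is standard and cheap.

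**What to change.** Before endline analysis, prespecify a ward-pair term in the linear mixed models alongside the clinic random intercept. State whether it is fixed or random, and match the degrees of freedom to the choice: about 9 if the pair is fixed. A random pair intercept estimated at zero collapses to the unpaired model, so the 9-df figures above apply to a fixed term. Report the unpaired model as a sensitivity analysis. If the sponsor prefers to break the pairs, the plan should say so in advance and give the reason.

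For binary outcomes, account for the pair in a way that tolerates pairs with no events, for example a random pair intercept, and do not require fixed strata. A pair has about 24 participants. Ignoring clustering and dropout, the chance of no event in a pair is 0.90²⁴ ≈ 8% at 10% prevalence and 0.95²⁴ ≈ 29% at 5%. Such pairs add nothing to a fixed-stratum logistic contrast.

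The cost is one random effect, or nine parameters if the pair is fixed, with fewer degrees of freedom and intervals up to about 6% wider if the pairing proves uninformative. No new data are needed. Trial status describes delivery as still under way, so the choice could be fixed before results are seen.
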